#### Patient Health Questionnaire 9 (PHQ-9)

Depressive symptoms will be measured with the PHQ-9 at the pre- and post-tests [22]. The questionnaire consists of nine items and includes the DSM-V criteria for a major depressive disorder. The items are rated on a four-point scale ranging from 0 “not at all” to 3 “nearly every day,” e.g., “Over the last two weeks, how often have you been bothered by: little interest or pleasure in doing things?” Scores range from 0 to 27, and cutpoints of 5, 10, 15, and 20 represent mild, moderate, moderately severe, and severe levels of depressive symptoms. The PHQ-9 is sensitive to change, has good sensitivity and specificity for detecting depressive disorders, and has adequate psychometric properties [37]. Furthermore, the questionnaire is often used with PLH [38]. This questionnaire will be used to screen participants on depressive symptoms and to measure change in depressive symptoms from baseline to the post-tests.

#### Center of Epidemiologic Studies Depression Scale (CES-D)

The CES-D [26] will be used to measure depressive symptoms during the past week. The questionnaire consists of 20 items, such as “During the past week: I felt sad.” Items are rated on a four-point scale ranging from 0 “rarely or none of the time (less than 1 day)” to 3 “most or all of the time (5-7 days).” Total scores can range from 0 to 60, and the cut-off score for clinical depression is 16. The internal consistency, reliability, and convergent validity of the CES-D are adequate [26, 39], and sensitivity and specificity are high [40]. Furthermore, the questionnaire is often used with PLH [41]. We will use this questionnaire to measure the change in depressive symptoms from the pretest to the post-tests.

#### Demographic variables and other information

A self-designed questionnaire will be used to ask participants about sex, age, educational level, nationality, marital status, sexual orientation, social support, disclosure of HIV positive status, alcohol and drug use, previous depressive and anxiety episodes, treatment of psychological symptoms, and physical health. This information will be used to describe the demographic and clinical characteristics of the sample. In the follow-up assessments, questions will be asked about the use of medication for psychological problems and treatment received from a psychologist or a psychiatrist since the start of the study. The use of medication and treatment received will be added as covariates in the analysis.

Furthermore, participants will complete a self-designed questionnaire about information regarding the HIV infection. Questions include time since the HIV diagnosis, how the infection occurred, symptoms of the infection, cluster of differentiation 4 (CD4) cell count, viral load, use of highly active antiretroviral therapy (HAART), medication adherence, and side effects of the medication. This information will be used to describe the HIV status and use of HAART by the sample.

#### Physical tension questionnaire

Physical tension will be measured with a self-designed 10-item questionnaire. Questions include difficulty to relax, ways to relax, and symptoms of physical tension (e.g., trembling hands, tense neck and shoulder muscles, and increased heart rate). Items can be answered on a three-point scale (no, sometimes, and yes). Higher scores reflect less physical tension.

#### Behavioral Activation for Depression Scale (BADS)

The subscale activation of the BADS [27] will be used to measure activation during the past week. The subscale consists of seven items that will be measured on a seven-point scale ranging from 0 “not at all” to 6 “completely,” e.g., “I am content with the amount and types of things I did.” Higher scores reflect greater levels of activation. The psychometric properties of the Dutch BADS are adequate [42].

#### Emotion Regulation Questionnaire (ERQ)

The reappraisal subscale of the ERQ [28] will be used to measure the cognitive reappraisal. The six items are rated on a scale ranging from 1 “strongly disagree” to 7 “strongly agree,” e.g., “When I want to feel less negative emotion, I change the way I’m thinking about the situation.” Higher scores indicate that cognitive reappraisal is often used to regulate emotions. The convergent and discriminant validity of the ERQ are adequate [28].

#### Cognitive Emotion Regulation Questionnaire (CERQ)

The subscales rumination, catastrophizing, positive refocusing, refocus on planning, positive reappraisal, and putting into perspective of the CERQ [29] will be used to measure the use of these cognitive coping strategies when thinking about having HIV. The subscales consist of four items each, which will be rated on a five-point scale ranging from 1 “(almost) never,” to 5 “(almost) always.” Higher scores on a subscale indicate that this cognitive coping strategy is often used when thinking about having HIV. Examples of items include “I keep thinking about how terrible it is that I have HIV” (catastrophizing) and “I think about pleasant experiences” (positive refocusing). The psychometric properties of the CERQ are adequate [43].

#### Crandell Cognitions Inventory (CCI)

The hopelessness subscale of the CCI [30] will be used to measure black and white depressive thoughts. The subscale consists of seven items that are rated on a five-point scale ranging from 1 “(almost) never” to 5 “(almost) always,” e.g., “I’ll never feel good again.” Higher scores indicate a higher frequency of black and white depressive thinking. The reliability and validity of the CCI are good [30, 44].

#### Coping self-efficacy questionnaire

Self-efficacy to cope with having HIV will be measured with a self-designed eight-item questionnaire ([name] & [name], unpublished questionnaire). The questionnaire is based on the Generalized Self-Efficacy Scale, which has a good reliability and validity [45]. Items will be measured on a five-point scale ranging from 1 “totally disagree” to 5 “totally agree,” e.g., “I have the necessary skills to deal with having HIV.” High scores reflect more self-efficacy to cope with having HIV.

#### Goal Disengagement and Reengagement Scale

Goal adjustment will be measured with the Goal Disengagement and Reengagement Scale [31]. We slightly adapted the scale so that questions will be asked regarding the disengagement and reengagement of goals that one has to stop pursuing because of having HIV. The scale consists of four items that measure goal disengagement (e.g., “If I have to stop pursuing an important goal in my life because I have HIV, it’s easy for me to reduce my effort toward the goal”) and six items that measure goal reengagement (e.g., “If I have to stop pursuing an important goal in my life because I have HIV, I start working on other new goals”). Items are measured on a five-point scale ranging from 1 “totally disagree” to 5 “totally agree.” Higher scores indicate more goal disengagement and reengagement. A question about new goals that have already been found will be added: “I have already found new goals.” This last question will be handled separately, with higher scores indicating that more new goals were found.

#### Behavioral Emotion Regulation Questionnaire (BERQ)

The subscales seeking distraction, actively approaching, seeking social support, and withdrawal from the BERQ ([name] & [name], unpublished questionnaire) will be used to measure the use of these behavioral strategies to cope with having HIV. Each subscale consists of four items that will be measured on a five-point scale ranging from 1 “never/hardly ever” to 5 “(nearly) always,” e.g., “I do other things to distract myself.” Higher scores on a subscale indicate that the strategy is often used to cope with having HIV. A previous study ([name] & [name], in preparation) has shown a good reliability of this questionnaire.

#### Personal growth questionnaire

Personal growth due to having HIV will be measured with a self-designed five-item questionnaire ([name] & [name], unpublished questionnaire). Items will be rated on a five-point scale ranging from 1 “not at all” to 5 “certainly,” e.g., “Because of having HIV I appreciate life more.” High scores indicate personal growth due to having HIV. In a previous study, the reliability of this questionnaire was adequate [15].

#### Generalized Anxiety Disorder 7 (GAD-7)

The severity of symptoms of anxiety will be investigated with the GAD-7 [32]. The questionnaire consists of seven items that are rated on a four-point scale ranging from 0 “not at all” to 3 “nearly every day,” e.g., “Over the last 2 weeks, how often have you been bothered by: feeling nervous, anxious or on edge.” Higher scores indicate more anxiety symptoms. The psychometric properties of the GAD-7 are adequate, and the scale also may be used as a screener for panic, social anxiety, and post-traumatic stress disorder [37].

#### Patient Health Questionnaire 2 and Patient Health Questionnaire 4 (PHQ-2 and PHQ-4)

The PHQ-4 [36] will be used to assess depressive and anxiety symptoms during the intervention or waiting period (for the mediational analysis). It consists of the first two questions of the PHQ-9 and the first two questions of the GAD-7. Items are rated on a four-point scale ranging from 0 “not at all” to 3 “nearly every day.” Higher scores indicate more pathology. The internal reliability, construct validity, and factorial validity are adequate [36]. The PHQ-2 [24] consists of the first two questions of the PHQ-9 and will be used by the HIV treatment centers to screen for depressive symptoms.

#### Hospital Anxiety and Depression Scale (HADS)

The HADS [25] will be used by some of the HIV treatment centers to screen for depressive symptoms. The HADS consists of an anxiety and a depression subscale, and each subscale consists of seven questions, e.g., “I still enjoy the things I used to enjoy.” Items are rated on a four-point scale, and the response categories are different for each question. Higher scores indicate more anxiety and depressive symptoms. The HADS is widely used and is a reliable and valid questionnaire to screen for anxiety and depressive symptoms [25, 46].

#### Life Events Scale

Life events will be assessed with the Life Events Scale [33]. The scale consists of 17 negative life events (e.g., divorce of parents), and participants indicate if they have not experienced the life event, experienced it longer than 1 year ago, or experienced it last year. For each of the two periods, a total score of negative life events will be calculated.

#### Motivation to start with the intervention

Three questions will be used to measure the motivation to start the intervention. Two questions will be asked regarding the expected usefulness of the intervention, and one question about the motivation to start with the intervention. Questions will be answered on a five-point scale, and the scores on the items will be summed.

#### Compliance

Two measures of program adherence will be used in this study. During the intervention, program adherence will be measured three times by asking participants whether they read the information on the website and performed the exercises. Furthermore, we will monitor whether the participant calls with the coach. These two measures will be handled separately.

#### Dropout and reasons for dropout

Two types of dropout will be investigated three times during the intervention and at T1, T2, and T3. We will register the participants who stopped using the intervention and the participants who did not complete the questionnaires. We will remind participants to fill in the questionnaires. When they drop out, we will ask them why they do not wish to participate anymore to investigate the reasons for dropout. We will examine the difference in dropout between groups and differences between participants who completed and stopped using the intervention.

#### Medical data

Medical data will be obtained from the Athena/SHM Cohort Study after consent from the participant. The ATHENA Cohort Study is maintained by Stichting HIV Monitoring, which is supported by the Dutch Ministry of Health via the National Institute for Public Health and Environment (RIVM). The data that will be used include the time since HIV diagnosis, medication use, CD4 cell count, and viral load.

#### User satisfaction questionnaire

At T1, we will ask participants about their satisfaction with the self-help program and the coach with a self-designed questionnaire. The questionnaire consists of 31 items to evaluate the intervention, for example, the components of the self-help program and the support from the coach. Open-ended and closed-ended questions will be used in the questionnaire. The questions for participants in the control group will concern the support from the coach (13 questions). The answers to these questions will be used to adjust the self-help program before implementing it.

### Statistical analyses

A two-tailed alpha of .05 will be used for significance testing. All analyses will be based on an intention-to-treat (ITT) analysis, which includes all participants who were randomized to one of the groups at the beginning of the study [47]. Baseline differences between conditions will be investigated with chi-square tests for categorical variables and ANOVAs for continuous variables.

To examine the effect of condition on the depressive symptoms at the post-tests, longitudinal multilevel regression analysis (LMRA) will be conducted [48]. A two-level model will be studied: time at level 1 and participants at level 2. The variable time will have four categories indicating the four time points (T0–T4). The baseline (T0) will be used as reference category. The independent variable is condition, the dependent variable is the score on the PHQ-9 or the CES-D, and several covariates will be included in the model (e.g., sex and age). Multiple imputation for missing data is not necessary in LMRA because it can include participants with missing data on one or more time points [48]. The existence of an effect of HIV treatment center will be investigated exploratory.

Furthermore, Cohen’s d will be calculated to indicate within- and between-group effect sizes [49]. In addition, clinically important differences for individual change in depressive symptoms will be examined. Change scores of 5 or more from the pretest to the post-tests will be considered as clinical important differences for the PHQ-9 [50].

With regard to all secondary outcomes, we will study the pre-treatment versus post-treatment changes by using the analyses described above for the PHQ-9 and the CES-D. To examine moderators of the treatment outcome, LMRA will be conducted. Potential moderators will be entered individually. Interaction effects will be investigated (e.g., time x condition x moderator). A limited number of cross-product interactions will be examined, and we will correct for multiple testing. Furthermore, the QUINT (Qualitative Interaction Trees [51]) method will be used to identify subgroups for which the intervention is most effective, by exploratory investigation of the multiple moderators.

Mediation will be tested by examining the indirect effect of the independent variable (condition) on the dependent variable (depressive symptoms) through the proposed mediators. Mediation analysis will be conducted by using latent difference score models, which are recommended with repeated measurements and multiple mediators [52]. These models focus on intra-individual change and individual differences in that change.

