## Methods/design

### Design

The study is a randomized controlled trial; participants will be randomly allocated to the intervention or the control group. Stratified randomization by treatment center and sex will be conducted. Stratification by sex is conducted, as there will be more male participants in the study, and the allocation of approximately the same number of females to the intervention group as to the control group is preferred. In addition, stratification by treatment center is being conducted because the number of (included) patients will differ among the treatment centers. Approximately equal allocation to each of the groups also in the small treatment centers, is important. This will be realized by creating random number tables for each treatment center, divided by sex. Randomization will take place in blocks of 12 participants for each treatment center. Males and females will represent separate blocks, with six males and six females for each treatment center, of which half will be randomly allocated to the intervention group, and half will be allocated to the control group. Participants, coaches, and researchers cannot be blind for allocation to conditions. Participants will be allocated to one of the conditions after the pretest. The random number tables will be created by an independent researcher, and the allocation sequence will be concealed from the main researcher, who enrolls and informs participants.

The design consists of multiple measurements, one pretest, three post-tests (two in the control group), and three assessments during the intervention/waiting period. Figure 1 shows a flow chart of the study design, and the SPIRIT Checklist is presented in Additional file 1. The study is approved by the medical ethics committee of the Leiden University Medical Center (LUMC; nr. P14.091). Online informed consent will be obtained from all participants.

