### Ethical precautions

Coaches will monitor the well-being of participants in both the intervention and control groups. Each week, they will ask how the participant is doing. When depressive symptoms worsen or when suicidal thoughts increase, the coach will discuss this with the participant. The coach can refer the participant to the general practitioner or the HIV treatment center, if necessary. The coach can discuss this with the researcher and the psychotherapist. When a participant is referred for more intensive treatment from a psychologist or psychiatrist, the participant may continue with the study. As this may influence the outcomes, the referral will be added as a covariate in the analysis.

Participants will complete questionnaires to assess depressive symptoms during the course of the study. When depressive symptoms of a participant increase, the researcher will notify the coach about this. The coach will discuss this increase of symptoms with the participant and will act appropriately. These guidelines are also described in the protocol for coaches.

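### Significance tests of baseline differences between the randomised arms are uninformative and should give way to a descriptive table, with covariates fixed on prognostic grounds (minor)

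*Protocol article*

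**What the plan says.** All references are to the protocol article.

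- **Baseline comparison (Statistical analyses).** "Baseline differences between conditions will be investigated with chi-square tests for categorical variables and ANOVAs for continuous variables". The same paragraph sets the general level: "A two-tailed alpha of .05 will be used for significance testing". A correction for multiple testing is mentioned in that section only for the moderator interactions.
- **Allocation (Design).** "Stratified randomization by treatment center and sex will be conducted", and "Participants will be allocated to one of the conditions after the pretest". On concealment: "the allocation sequence will be concealed from the main researcher, who enrolls and informs participants". The Procedure section gives the same order, with T0 first and allocation next.
- **Covariates of the primary model (Statistical analyses).** "several covariates will be included in the model (e.g., sex and age". An effect of treatment centre is to be looked at in an exploratory way only.
- **Other covariates.** Ethical precautions adds referral: "As this may influence the outcomes, the referral will be added as a covariate in the analysis". The section on demographic variables adds medication for psychological problems and treatment received since the start of the study. All of these arise after randomisation.
- **Purpose.** The section on demographic variables says those data serve to describe the sample. No purpose is given for the baseline tests.

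**The concern.** A test of a baseline difference asks whether the arms were drawn from the same population. Under concealed random allocation after the baseline measurement, the design already answers that. The p-value therefore says nothing about what matters for the analysis, which is whether an imbalance lies in a variable that predicts depressive symptoms. A small p-value in a variable unrelated to outcome is noise. A large p-value in a strong predictor is no reassurance.

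Two things are at stake. The trial report may present chance findings as baseline differences, or their absence as proof of comparability. In addition, the covariates are given by example and the use of the test results is not stated, so an analyst could keep to the text and still adjust for whatever tested significant. The adjusted effect would then depend partly on chance imbalance instead of on prognostic strength.

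**Working it through.** **1. The plan's own figures.** The article gives no figure for the baseline tests; the sample size section only supplies the arm sizes. For d = 0.50, two-sided alpha .05 and power .80, the two-sample t-test needs 63.77, so 64 per group, as stated. Allowing for 15% dropout, 64 / 0.85 = 75.3 against 75 stated, a rounding difference. The aim of at least 200 participants gives 100 per arm.

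**2. Is the null true by design?** T0 precedes allocation, allocation is random, and the sequence is concealed from the researcher who enrols. A T0 difference between arms can then arise only by chance.

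**3. How many tests?** Not stated, so this is an assumption with a range. The section on demographic variables lists about 20 to 22 characteristics, depending on how compound items are split. Adding the T0 scales, subscales and HIV items from the Assessments section gives about 44 without sex. That count is an upper-end assumption; 10 is taken as a modest lower value.

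**4. False flags.** For k independent tests at .05, P(at least one) = 1 − 0.95^k. The expected number is 0.05 × k, whatever the correlation. The correlated columns come from a simulation of equicorrelated normal test statistics (200,000 draws).

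| k | Expected false flags | Independent | Correlation 0.3 | Correlation 0.5 |
|---|---|---|---|---|
| 10 | 0.5 | 0.40 | 0.35 | 0.29 |
| 20 | 1.0 | 0.64 | 0.54 | 0.42 |
| 30 | 1.5 | 0.79 | 0.66 | 0.51 |
| 44 | 2.2 | 0.90 | 0.77 | 0.59 |

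Many T0 measures are related (two depression scales, anxiety, hopelessness, coping), so the correlated columns are realistic. Sex is balanced by stratified blocks, so its own chance of a flag is well below 5%.

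**5. What passes as no difference.** The largest standardised difference that is not significant is about 1.96 × √(2/n).

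- n = 100 per arm: 1.96 × √0.02 = 0.28 SD.
- n = 75 per arm: 1.96 × √0.0267 = 0.32 SD.

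For scale, suppose such a variable correlates 0.3 to 0.6 with the outcome (an assumption). In a plain comparison of post-test means, leaving it out shifts the difference by 0.28 × 0.3 = 0.08 SD to 0.28 × 0.6 = 0.17 SD, against a design effect of 0.50. The shift is smaller where the T0 score already carries that information.

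**6. Link to the covariates.** Sex, age, referral, medication and treatment received are all named without reference to a baseline test. No sentence connects the tests to the choice of covariates, and none excludes such a connection.

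**The case against.** The strongest case against the point has five parts.

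- **Covariate selection is not stated.** A reader might infer that the baseline p-values will decide which covariates enter the model, or are the only data-driven route to that decision. The article does not support this. It names its covariates independently of the tests, and other planned looks at the data (centre effects, dropout comparisons) could prompt an added covariate just as well. This objection stands; only the weaker statement, that nothing rules it out, can be kept.
- **A false flag is not certain.** A reader might also infer that one or more variables are bound to be flagged. Step 4 shows a probability, and it depends on an unstated number of tests and their correlation. This stands too.
- **The open covariate list is missing detail.** A condensed article may leave the full list to a protocol or analysis plan that is not at hand. This stands, and the open list alone is no finding. The baseline tests are different, because the article affirmatively plans them.
- **The main predictor is already in the model.** T0 is the reference category of time, so the baseline depression score is in the analysis whatever its p-value, and sex and age are named. This stands and limits the harm.
- **The tests could check the randomisation.** Nobody is blind to condition, and blocks of fixed size within centre and sex might let late allocations be guessed. A baseline comparison is then a crude check. The article states no such purpose, and a descriptive table shows a gross irregularity equally well. Little of this stands.

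**Conclusion.** The planned tests assess a null hypothesis that the design makes true, and they cannot show whether an imbalance matters. With 10 to 44 tests, the chance of at least one false flag is about 0.29 to 0.90 across the assumptions used, while imbalances of up to 0.28 SD (100 per arm) or 0.32 SD (75 per arm) go unremarked. These figures assume that the general .05 level applies to each test and that concealment holds. The test counts and correlations are assumptions, not figures from the article.

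The severity is minor. The tests alone do not bias the primary estimate and do not change its alpha, the power or the sample size. Harm to the primary result would need a further step, selection of covariates by baseline p-value, which the article neither plans nor excludes.

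The related point on covariates is concrete. Allocation is stratified by centre and sex, yet sex appears in the model only as an example and centre only as an exploratory question.

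**What to change.** 1. Replace the sentence on baseline tests with one such as: *T0 characteristics will be presented by arm as means and standard deviations or as counts and percentages, without significance tests.* Standardised differences may be added.
2. State that the covariates of the primary longitudinal multilevel model are pre-randomisation variables chosen on prognostic grounds before outcomes are compared by arm, and that baseline p-values play no role. Include both stratification factors and age. With 23 centres and about 200 participants (200 / 23 ≈ 9 per centre), centre could enter as a random effect in place of the exploratory look alone. Referral, medication and treatment received are post-randomisation variables and do not belong in this set.
3. Do not add the T0 depression score as a separate covariate while T0 remains an outcome occasion, because the same measurement would then stand on both sides of the model. Either leave baseline where it is, or restructure the model with T0 as a covariate only and the post-tests as outcomes.

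The cost of items 1 and 2 is two or three sentences and somewhat less analysis work. Restructuring under item 3 would be a larger change, but it is optional. Recruitment is complete according to Trial status, which is no obstacle because only analysis text changes. Sample size, power and alpha stay as they are.

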#### Support from a coach

Participants in the intervention group will be allocated to a coach, who will provide motivation and support throughout the program. During the first telephone contact, the coach will introduce the program, motivate the participant, and address technical aspects. Once a week, a prescheduled telephone call of approximately 15 minutes will be arranged between the participant and the allocated coach. Coaching will be provided through queries about the participant’s progress, motivational remarks, support in case problems are encountered, and encouragement to continue the program. Coaching will not include formal psychotherapy and will be provided until the participant completes the program or for a maximum of 10 weeks. If the participant is not finished with the program after 10 weeks, the coaching will end, but the participant can continue the program.

Participants in the control group will also be allocated to a coach, who will provide minimal support over 8 weeks. Participants will have a pre-scheduled weekly telephone call of approximately 5 minutes with the coach. The coach will address the well-being of the participant. Coaches will try to prevent participant dropout and monitor their depressive symptoms. When depressive symptoms or suicidal thoughts increase, the coach will act appropriately (see ethical precautions).

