A protocol for coaching will be used, with guidelines available for the provision of support. Coaches will receive a short training to inform them about the study and the coaching procedures. After each telephone call, coaches will note the elements that were used during the call (e.g., motivation, support) to monitor treatment integrity. Coaches will be Master students in clinical psychology or individuals with a Master’s degree in the field of psychology. The coaches will have completed clinical courses during their Master’s degree program in which they learned communication skills, interview techniques, and treatment strategies. In addition, coaches will be selected in a personal interview on the basis of adequate communication skills for the support and motivation of participants. Coaches will be supervised by the researchers and a psychotherapist. Once every 2 weeks (every week during the first month of the study), the coaches and the main researcher will hold an intervision meeting. Coaches can discuss difficulties and questions with each other and the researcher. If a problem arises between intervision sessions, the coach may contact the researcher. The researcher and the coach can consult a psychotherapist if necessary.

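### The two-level model has no term for coach, so the standard error of the condition effect may be too small if outcomes vary by coach within arm or differently by arm

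*Protocol article*

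**What the plan says.** Under Statistical analyses the protocol article sets the level structure outright: "A two-level model will be studied: time at level 1 and participants at level 2". The only grouping factor considered beyond the participant is the clinic: "The existence of an effect of HIV treatment center will be investigated exploratory". Coach appears neither in the model nor in the Sample size section.

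Under Support from a coach, both arms receive coaching:
- Intervention arm: "Participants in the intervention group will be allocated to a coach, who will provide motivation and support throughout the program". The contact is individual and regular: "Once a week, a prescheduled telephone call of approximately 15 minutes will be arranged between the participant and the allocated coach". It lasts until the programme is completed, or 10 weeks at most.
- Control arm: "Participants in the control group will also be allocated to a coach, who will provide minimal support over 8 weeks". These calls are also weekly but last about 5 minutes and deal with well-being.

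There is more than one coach: "Coaches can discuss difficulties and questions with each other and the researcher". The section does not give their number or caseload, or say whether the same people coach both arms. The Background and the description of the intervention present coaching as something that should raise effectiveness and reduce attrition.

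**The concern.** Participants who share a coach may have correlated outcomes after randomisation. The clusters are caseloads, since coaching is one-to-one by telephone. A model with only time and participant levels counts every participant as a separate piece of information about the condition effect. Where part of the outcome variation sits between coaches within an arm, the effective sample is smaller than the model assumes. Confidence intervals are then too narrow, and the nominal level ("A two-tailed alpha of .05 will be used for significance testing") is not the level achieved.

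This is plausible here. Support is repeated for up to 10 weeks, the article credits it with part of the effect, and the coaches are Master students or psychology graduates given a short training. Because the coach does more in the intervention arm, an effect that differs by arm is the natural possibility to guard against.

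**Working it through.** **Inputs from the article.** Effect size 0.50, two-sided alpha .05, power .80, 64 completers per group, 15% dropout, 150 allocated and a target of at least 200 (Sample size). Two levels, no coach term (Statistical analyses).

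**Assumptions, because the article gives no values.** Participants per coach within an arm, m = 10 to 20. Coach ICC = 0.01 to 0.05, on the scale of the contrast being tested. Equal arms and equal caseloads.

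**1. The plan's own figure.** A two-sample t-test with d = 0.50, alpha .05 and power .80 needs 63.8, so 64 per group (power at 64 is 0.801). Then 64/0.85 = 75.3, against the stated 75. The figure reproduces with independent participants, so it contains no allowance for coach.

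**2. Coaches confined to one arm.** The design effect is DE = 1 + (m − 1) × ICC.
- Clustering in both arms, separate coaches: the true standard error is k times the model's, with k = √DE.
- Clustering in the intervention arm only: the variance of the difference is proportional to DE + 1 instead of 2, so k = √((DE + 1)/2).
- Actual type I error = 2 × (1 − Φ(1.96/k)).

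| m | ICC | DE | Type I error, intervention arm only | Type I error, separate coaches in both arms |
|---|---|---|---|---|
| 10 | 0.01 | 1.09 | 5.5% | 6.0% |
| 20 | 0.01 | 1.19 | 6.1% | 7.2% |
| 10 | 0.05 | 1.45 | 7.7% | 10.4% |
| 20 | 0.05 | 1.95 | 10.7% | 16.0% |

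Worked example, last row: (1.95 + 1)/2 = 1.475, k = 1.2145, 1.96/1.2145 = 1.614, giving 10.7%. For both arms, k = √1.95 = 1.396, 1.96/1.396 = 1.404, giving 16.0%.

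**3. Coaches serving both arms.** A coach effect that is identical in both arms cancels from the difference when caseloads are balanced, while the model still counts it as residual variance. A simulation with 64 per arm, 8 coaches (8 participants per coach per arm), ICC 0.05 and 20,000 runs gave these type I errors:
- different coaches in each arm: 0.092 (formula: DE = 1.35, also 0.092);
- same coaches, half of the coach variance specific to the arm: 0.065;
- same coaches, identical effect in both arms: 0.045.

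Inflation therefore depends on how coaches are allocated and on whether their effect differs by arm. In the last case the two-level model is slightly conservative.

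**Limit of the check.** The calculation compares means at one post-test. The planned model takes T0 as its reference, so the inflation in the time-by-condition contrast also depends on the within-person correlation, which the article does not give.

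**The case against.** Several points on the other side have weight.

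- **The inflation is not established.** A reader might infer that the standard error is understated as a matter of fact. The article does not support that. It reports no coach variance and leaves open whether coaches serve both arms, and in one of the possible arrangements type I error does not rise at all.
- **It is not bias.** A reader might also infer that a few good or poor coaches would be mistaken for a programme effect. Coaching is a designed part of the intervention, so programme plus coaching is the intended contrast. Omitting coach affects the precision claimed and how far the result carries over to other coaches. It does not by itself bias the estimate.
- **Coach variance may be small.** Coaching excludes formal psychotherapy and follows a protocol. Coaches are selected by interview, trained, supervised and meet regularly, and the main content is a standard website. Coaching also ends by week 10, so a coach effect must persist to influence the later follow-up that the sample size targets. All this makes a low ICC more plausible but does not show that it is zero.
- **Few coaches.** At 20 per coach, 64 to 100 intervention participants means about 3 to 5 coaches (64/20 = 3.2; 100/20 = 5), too few for a stable variance estimate. This stands, and it is why the adjusted model should not be imposed as primary.
- **Detail for the analysis plan.** An article can leave secondary random effects to the analysis plan. But this one states the levels of the main model and names the one other grouping factor to be explored, so the omission of coach lies in what it fixes.

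**Conclusion.** The point holds in conditional form. The stated model leaves out a source of dependence that the trial's own delivery creates. Type I error exceeds .05 if outcomes vary by coach and coaches are nested in arm or their effect differs by arm. Under the assumed caseloads and ICCs the excess runs from negligible (5.5%) to material (10.7% with clustering in the intervention arm only, 16.0% with separate coaches in each arm). The upper ends need a caseload of 20 and an ICC of 0.05 together. With the same coaches in both arms and an identical effect, there is nothing to correct. The article does not allow a choice among these cases, which is itself a reason to state the allocation. This is a worthwhile, inexpensive improvement and does not invalidate the primary analysis.

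**What to change.** 1. State how many coaches there were, their caseloads, and whether the same coaches served both arms.
2. Prespecify a coach-adjusted version of the condition model. Use a random coach effect, partially nested in the intervention arm. If coaches served both arms, cross coach with condition and include a random coach-by-condition term. Apply a small-sample degrees-of-freedom correction.
3. Report it, with the estimated coach variance, beside the main result. Make it the primary model only if there are enough coaches for stable estimation, and fix that decision before outcomes are seen by condition.

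The cost is analysis wording, a little more analysis work and slightly wider confidence intervals. Recruitment is complete according to Trial status, so the analysis is where this can still be handled. Coach identity should be recoverable, since each participant is allocated to a coach and "After each telephone call, coaches will note the elements that were used during the call". The article does not say expressly that those notes identify the coach, so this should be confirmed.
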